#### Procedure

The participants will be individuals with type 1 diabetes who regularly attend consultations in the Clinical Management Unit of Endocrinology and Nutrition of 2 hospitals (tertiary care) and a specialty center (secondary care) of the Andalusian Health Service of the province of Malaga (Spain) who voluntarily choose to participate in the study. The participants will not receive any type of economic or material remuneration.

Patients will be recruited through information posters placed in the visible areas of the Units, inviting them to participate in the study, either directly by sending an e-mail or through their physician. Those interested in participating will be evaluated by a psychologist from the research group who will assess the inclusion and exclusion criteria. Depressive symptoms will be evaluated with the Beck Depression Inventory-FastScreen (BDI-FS) [43] Patients with a BDI-FS score greater than or equal to 4 and less than 13 who meet the rest of the inclusion criteria and none of the exclusion criteria will sign the informed consent. All questions about the study will be answered, and the necessary aspects clarified, ensuring that the participant has understood everything he or she has read. The participants will then be prepared to begin the study and the initial assessment will be conducted.

Once the sample has been randomized, the participants will be notified of the group to which they have been assigned by e-mail. Those assigned to the CG will be given encouragement while they wait to begin treatment after the TG has completed the treatment (Fig 1).

**Fig 1 pone.0274551.g001:**
[figure not shown]
SPIRIT schedule of enrolment, intervention and assessments. Note: -t1, Eligibility screen, Informed consent; t1, baseline assessment; t2, post 8-week intervention; t3, 3-month follow-up; t4, 6-month follow-up; t5, 12-month follow-up; t6, participants complete treatment and follow-up in both the TG and the CG.

#### Intervention

The web page will include the 9 sessions that comprise the CBT-based treatment (Table 1). The sessions will be weekly. Each week, the participant will find a brief summary of the previous session and an introduction to the topic being covered, with an explanation of the new session. The participant will then be provided with the new information (the subject matter) and various examples will be included to facilitate understanding. Once the information is introduced, a summary of the key ideas of the session will be presented and a short evaluation will assess the subject’s understanding. At the end of the session, the person will have the key ideas and a self-assessment of the session. Finally, the participant will receive an explanation of the task to be completed and forwarded to the therapist with an example of how the task should be carried out. The therapist will respond and provide feedback on the completed assignment, but no personal advice will be given. Each session will need to be completed in order to have the following session available. In addition, the participant will have a bibliography of each of the topics covered. Each session will last 20–30 minutes.

**Table 1 pone.0274551.t001:** Treatment sessions.

Session	Topic
1	What is depression? Relationship between cognitions, behavior and emotions. Relationship between diabetes and depression.
2	Relationship between stress and diabetes. Use of relaxation and physical exercise for the management of stress and diabetes.
3	Coping in diabetes. How to face the fears associated with diabetes (short-/medium- and long-term complications).
4	Identification, definition and resolution of problems. The demands of daily self-care.
5	Pleasurable activities. Incorporation of a physically and mentally healthy lifestyle plan.
6	Cognitive restructuring. Modification of beliefs and cognitive errors in diabetes.
7	Social skills: communication style. Working towards an assertive communication style. Communication with family, friends and medical professionals.
8	Importance of support. Searching for sources of support regarding diabetes.
9	Relapse prevention.

Therapists will send e-mails to the TG participants to encourage them to continue their efforts and they will be called if there is no response to these e-mails. Halfway through the program, their opinions about it will be sought (doubts, suggestions for improvement). This is intended to motivate the participants in order to improve adherence and minimize the risk of drop out.

The CG (waiting list) participants will receive a telephone call or e-mail informing them of the next program start date. In the event that during the study an individual (CG or TG) is found to have a worsening depressive mood (severe depression or suicidal ideation), the participant would discontinue the study and his or her physician would be notified in order to refer the individual to the Clinical Management Unit of Mental Health of the Andalusian Health Service.

Protocol amendments: Important protocol modifications will be reported to the researchers, the University of Malaga and the protocol registry.

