## Material and methods

### Study design and participants

This study is a longitudinal randomized control-group pretest-posttest clinical trial (S1 Table). Patients with type 1 diabetes who present depression (mild to moderate) and meet the inclusion criteria will be randomized through a computer program to 2 groups. The treatment group (TG) will receive the 9-week Web-based treatment, while the control group (CG) will comprise patients on the waiting list. Evaluations in the TG will be conducted at the beginning of the program (baseline), at completion and during follow-up (3, 6, and 12 months) after treatment. For ethical reasons, the CG will receive the Web-based treatment once the TG intervention has been completed. The CG will thus be assessed at the beginning and at the end of the TG treatment. At this point, the CG will begin treatment, provided the participants still meet the eligibility criteria, and will have their corresponding evaluations. The assessments will be conducted in person.

The participants will be individuals with type 1 diabetes from the province of Malaga (Spain) who meet the following criteria:

○ Inclusion criteria: medical diagnosis of type 1 diabetes ≥ 1 year; over 18 years of age; psychological diagnosis of mild/moderate major depressive disorder, dysthymia or depressive symptomatology; no concomitant pharmacological treatment that could modify blood glucose values or depressive symptomatology; no psychological treatment at the present time; absence of the following: chronic renal failure, impaired liver function tests, active thyroid disease (except correctly substituted hypothyroidism), current pregnancy or acute ketosis decompensation at the beginning of the study; Internet access.○ Exclusion criteria: type 2 diabetes; women who are pregnant or planning to become pregnant; severe macrovascular or microvascular complications; diagnosis of major depressive disorder with risk of suicide; non-collaboration (no signed informed consent); presenting a disabling psychiatric disorder; psychosis; no Internet access.

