## Results assessed

The variables set out below will be collected at each assessment point, with the exception of personality, which will only be collected at the beginning of the study (Table 2).

**Table 2 pone.0274551.t002:** Variables evaluated in the study.

Variable	Measurement instrument	Measurement time
Sociodemographic data, habits, diabetes support and previous Mental Health treatment.	Structured interview	Baseline, post-treatment, 3 months, 6 months, 1 year
Clinical data and glycemic control	Record sheet	Baseline, post-treatment, 3 months, 6 months, 1 year
Depressive symptoms	Beck Depression Inventory FastScreen (BDI-FS, Sanz, Izquierdo & García-Vera, 2011)	Baseline, post-treatment, 3 months, 6 months, 1 year
Depression	Structured Clinical Interview for DSM-V Major Depression Episode (SCID-5-CV) (First, Williams, Karg & Spitzer, 2016).	Baseline, post-treatment, 3 months, 6 months, 1 year
Fear of hypoglycemia	Fear of Hypoglycemia questionnaire (FH-15) (Anarte et al., 2011)	Baseline, post-treatment, 3 months, 6 months, 1 year
Diabetes-related distress	Diabetes-related distress. The Spanish version (Fisher, Glasgow, Mullan, Skaff & Polonsky, 2008) of the Diabetes Distress Scale (DDS) by Polonsky et al. (2005) will be used.	Baseline, post-treatment, 3 months, 6 months, 1 year
Quality of life	Diabetes Quality of Life Questionnaire (DQOL) (The DCCT Research Group, 1988).	Baseline, post-treatment, 3 months, 6 months, 1 year
Anxiety	Anxiety through the Spanish version (Seisdedos, 1988) of the State-Trait Anxiety Inventory (Spielberger, Gorsuch & Lushene, 1982).	Baseline, post-treatment, 3 months, 6 months, 1 year
Coping	Coping with the Spanish version (Crespo & Cruzado, 1997) of the COPE Inventory (Carver, Scheier & Weintraub, 1989).	Baseline, post-treatment, 3 months, 6 months, 1 year
Treatment adherence	Diabetes Self-Care Inventory-Revised questionnaire (SCI-R). The Spanish version will be used to evaluate treatment adherence (Jansà, Vidal, Giménez, Conget, Galindo et al, 2013).	Baseline, post-treatment, 3 months, 6 months, 1 year
Personality	Personality through the Millon Clinical Multiaxial Inventory-III (MCMI-III) (Millon, Davis and Millon, 1997), Spanish version by Cardenal and Sánchez (2007)	Baseline

Through a structured interview, sociodemographic data, medication taken and healthy and harmful habits will be recorded, as well as previous Mental Health treatment and diabetes-related support.

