Clinical data and glycemic control will be collected through the medical record form of the visit to the physician and the data provided by the participant.

The primary variable is depression. Depressive symptoms during the previous 2 weeks will be assessed through a self-administered 7-item questionnaire (0–3), the BDI-FS [43]. For the diagnosis of depression, the Structured Clinical Interview for Major Depression Episode of the DSM-V will be used [44].

Among the secondary variables, fear of hypoglycemia will be evaluated with the Fear of Hypoglycemia questionnaire (FH-15) [45], which consists of 15 negative items on a Likert-type scale (1–5), and diabetes-related distress using the Spanish version [46] of the Diabetes Distress Questionnaire (DDS) by Polonsky et al., [47] which has 16 Likert-type items (1–5). The DDS provides a total distress score and 4 specific scores: affective distress; distress associated with the doctor-patient relationship; regimen-related distress and interpersonal distress. Quality of life will be assessed with the Diabetes Quality of Life Questionnaire [48], which evaluates quality of life specifically in individuals with diabetes mellitus. The Spanish version [49] has 43 questions (1–5) and 4 subscales: Dissatisfaction, Impact, Social/vocational concern and Concern for future aspects. Anxiety will be addressed using the Spanish version [50] of the State-Trait Anxiety Inventory (STAI) [51]. The STAI consists of 2 scales: State Anxiety (STAI-S) and Trait Anxiety (STAI-T). Each scale includes 20 self-administered items (0–3). Coping will be evaluated with the Spanish version [52] of the COPE inventory [53], composed of 5 scales assessing problem-centered coping, another 5 scales measuring emotion-centered coping, and 3 scales measuring less useful coping responses. Adherence to treatment will be evaluated with the 15-item (1–5) Spanish version of the Diabetes Self-Care Inventory-Revised questionnaire [54]. Personality will be evaluated using the Millon Clinical Multiaxial Inventory-III Spanish version [55]. This questionnaire contains 175 items with true or false answers. It consists of 11 basic personality scales, 3 pathological characteristics scales, 7 moderate syndrome scales and 3 severe syndrome scales.

The results of the trial will be published in peer-reviewed journals and presented in conferences.

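### The rule for worsening depression ends study participation and not only the web program, so later primary-outcome scores are lost for an outcome-related reason; the expected bias is small and the fix is cheap

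*Protocol article*

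**What the plan says.** All references are to the Protocol article.

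- **Intervention.** Worsening in either arm, defined as severe depression or suicidal ideation, leads to exit and referral: "the participant would discontinue the study and his or her physician would be notified". No BDI-FS cut-off is attached to the word severe.
- **Results assessed.** "The primary variable is depression", with symptoms measured by the BDI-FS. On timing: "The variables set out below will be collected at each assessment point" (personality excepted).
- **Study design and participants.** The TG is assessed at baseline, "at completion and during follow-up (3, 6, and 12 months) after treatment". For the waiting-list arm: "The CG will thus be assessed at the beginning and at the end of the TG treatment". The CG then starts the program if its members are still eligible.
- **Procedure.** Entry is limited on the outcome scale itself: "Patients with a BDI-FS score greater than or equal to 4 and less than 13".
- **Intervention, on contact.** TG participants send in weekly tasks: "The therapist will respond and provide feedback on the completed assignment, but no personal advice will be given". They also receive e-mails, and "they will be called if there is no response to these e-mails". The CG receives a call or e-mail about the start date.
- **Statistical analysis.** Two analysis sets are named: those who complete the program, and one described as according to the protocol.

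**The concern.** The trigger for leaving and the primary outcome are the same construct. Whoever leaves under this rule is, by definition, at the bad end of the depression scale, so the missing scores are not a random subset.

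The wording cannot be read as stopping treatment only. The rule names the CG, whose members have no program to stop while they wait. Nor is this a detail that an analysis plan could supply later, because no analysis can recover scores that the protocol stopped anyone from collecting.

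Two things are at stake. The first is some distortion of the TG-CG comparison. The second is that the trial would not learn what became of participants who deteriorated during or after an untested web treatment.

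**Working it through.** **Step 1. Which scores are lost.** This depends on when worsening is found.

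| Worsening found | Score lost | Analysis affected |
|---|---|---|
| Between baseline and the post-treatment visit | Post-treatment BDI-FS and all later scores | Randomised TG-CG comparison, and follow-up |
| At the post-treatment visit | Later scores only; that visit's score is on record | Uncontrolled within-group course |
| After the post-treatment visit | Later scores only | Uncontrolled within-group course |

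The first row needs an unscheduled finding, because the article describes no mood assessment between visits in either arm. The lower rows cannot touch the randomised comparison, because the CG is a control only up to the end of TG treatment.

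**Step 2. Inputs for the size.** From the document: 28 per group (Sample size calculation) and entry at BDI-FS 4 to 12 (Procedure). The document gives no expected exit rate and no post-treatment mean or SD, so the rest is assumed:
- severe means BDI-FS 13 or more, cut at 12.5 on a continuous scale;
- CG mean/SD of A 6.5/3, B 7.5/3.5, or C 8.5/4 (extreme), the same mid-course as post-treatment;
- correlation of 0.6 between the mid-course and post-treatment scores;
- detection of those at 13 or more: 50% in the TG, 20% in the CG.

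**Step 3. Formula.** Let z = (12.5 − mean)/SD, p = 1 − Φ(z), and φ the normal density. If a share f of those above the cut leaves mid-course, the post-treatment mean of those who remain falls, in SD units, by

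shift = 0.6 × f × φ(z) / (1 − f × p).

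**Step 4. No true effect (both arms have the CG distribution).**

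| | z | p | φ(z) | TG shift, f = 0.5 | CG shift, f = 0.2 | Spurious d |
|---|---|---|---|---|---|---|
| A | 2.00 | 0.0228 | 0.0540 | 0.0162/0.9886 = 0.016 | 0.0065/0.9954 = 0.007 | about 0.01 |
| B | 1.43 | 0.0766 | 0.1438 | 0.0431/0.9617 = 0.045 | 0.0173/0.9847 = 0.018 | about 0.03 |
| C | 1.00 | 0.1587 | 0.2420 | 0.0726/0.9207 = 0.079 | 0.0290/0.9683 = 0.030 | about 0.05 |

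A simulation on scores rounded and clipped to 0-21 gives the same values: 0.01, 0.03 and 0.05. The expected number lost per 28 (28 × p × f) is 0.32, 1.07 and 2.22 in the TG and 0.13, 0.43 and 0.89 in the CG. Swapping the detection rates reverses the sign.

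**Step 5. Direction when the true d is 0.50.** In scenario C the TG mean is half an SD lower, so z = 1.5, p = 0.0668 and φ(z) = 0.1295. In units of the unselected SD, observed d ≈ 0.50 − CG shift + TG shift:
- TG 50%, CG 20%: 0.50 − 0.030 + 0.040 = 0.51
- TG 50%, CG 50%: 0.50 − 0.079 + 0.040 = 0.46
- TG 20%, CG 50%: 0.50 − 0.079 + 0.016 = 0.44

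The effect can therefore be inflated slightly or diluted, depending on who is detected. With d scaled to the SD of the remaining scores, 50%/20% detection gives 0.50, 0.50 and 0.52 for A, B and C.

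**Step 6. Against sampling error.** The standard error of d at 28 per arm and no effect is √(2/28) = 0.267. The extreme scenario gives 0.05/0.267 = 0.19 of one standard error.

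**Step 7. Follow-up.** Take a true d of 0.50, and suppose every TG participant at 13 or more after treatment leaves. The TG post-treatment mean of those who stay moves from 5.06 to 5.01, 5.82 to 5.60, or 6.59 to 6.04. Multiplying by 0.6, the 3-month mean looks better by about 0.03, 0.13 or 0.33 points.

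**The case against.** The strongest reply is that the route to harm is narrow. Entry is restricted to mild or moderate depression, suicide risk with major depression is excluded, and the randomised comparison loses a score only through an unscheduled finding before the post-treatment visit. All of that stands and is why the point is minor.

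It can also be said that exit visits and follow-up of withdrawals are details a journal article leaves to the full protocol. That is fair for an exit score, but not for the rule itself, which is stated and names the study as what ends.

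Third, scores after referral mix in the effect of mental-health care, so keeping them is a choice of estimand. True, but collecting them rules out no estimand, whereas not collecting them does.

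Fourth, the completer analysis already drops TG participants who stop the program, whatever is collected. That is a separate matter and adds no weight here, but it does mean that the wording change alone would not alter the stated TG analysis.

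Two stronger readings are tempting:
- **Material bias in favour of the program.** The TG has more contact between visits, so a reader might infer that its worsening is detected more often. The rule names both arms, and differential detection is an inference that the article neither states nor excludes.
- **Larger figures.** Removing people by their post-treatment score itself, at the same 50%/20% detection, gives a spurious d of 0.02, 0.05 or 0.09. But in that case the score is already on record, and nothing in the article says to discard it.

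**Conclusion.** The point holds as a minor one. A stated rule removes participants from observation because of their level on the primary variable, and their later scores are lost as a result. The randomised comparison is exposed only to worsening found between baseline and the post-treatment visit. The plausible distortion there is about 0.01 to 0.05 in d under no effect, with either sign possible and well inside sampling error. These figures rest on assumed means, SDs, correlation, detection rates and cut-off. They are illustrations, not limits, and they leave out exits triggered by suicidal ideation at lower scores. The documents do not support a claim of large or one-directional bias. The case for change is that the loss is avoidable, that the trial should know the outcome of those who got worse, and that the remedy costs little.

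**What to change.** - Keep the notification and referral. Change the rule so that the participant stops the web program (or, in the CG, does not start it) but stays in the study. For the CG this fits the existing condition that eligibility must still be met at crossover.
- Record the BDI-FS when worsening is found.
- With consent, keep the participant in the scheduled post-treatment and follow-up assessments.
- Include these participants in an as-randomised analysis of the post-treatment BDI-FS, beside the two sets already named.
- Report by arm how many worsened and when this was found.

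The cost is a short wording change, one extra seven-item questionnaire at detection, and visits that are already scheduled. The downside is that later scores may reflect care received after referral, so that care should be recorded and reported alongside them.

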## Results assessed

The variables set out below will be collected at each assessment point, with the exception of personality, which will only be collected at the beginning of the study (Table 2).

**Table 2 pone.0274551.t002:** Variables evaluated in the study.

Variable	Measurement instrument	Measurement time
Sociodemographic data, habits, diabetes support and previous Mental Health treatment.	Structured interview	Baseline, post-treatment, 3 months, 6 months, 1 year
Clinical data and glycemic control	Record sheet	Baseline, post-treatment, 3 months, 6 months, 1 year
Depressive symptoms	Beck Depression Inventory FastScreen (BDI-FS, Sanz, Izquierdo & García-Vera, 2011)	Baseline, post-treatment, 3 months, 6 months, 1 year
Depression	Structured Clinical Interview for DSM-V Major Depression Episode (SCID-5-CV) (First, Williams, Karg & Spitzer, 2016).	Baseline, post-treatment, 3 months, 6 months, 1 year
Fear of hypoglycemia	Fear of Hypoglycemia questionnaire (FH-15) (Anarte et al., 2011)	Baseline, post-treatment, 3 months, 6 months, 1 year
Diabetes-related distress	Diabetes-related distress. The Spanish version (Fisher, Glasgow, Mullan, Skaff & Polonsky, 2008) of the Diabetes Distress Scale (DDS) by Polonsky et al. (2005) will be used.	Baseline, post-treatment, 3 months, 6 months, 1 year
Quality of life	Diabetes Quality of Life Questionnaire (DQOL) (The DCCT Research Group, 1988).	Baseline, post-treatment, 3 months, 6 months, 1 year
Anxiety	Anxiety through the Spanish version (Seisdedos, 1988) of the State-Trait Anxiety Inventory (Spielberger, Gorsuch & Lushene, 1982).	Baseline, post-treatment, 3 months, 6 months, 1 year
Coping	Coping with the Spanish version (Crespo & Cruzado, 1997) of the COPE Inventory (Carver, Scheier & Weintraub, 1989).	Baseline, post-treatment, 3 months, 6 months, 1 year
Treatment adherence	Diabetes Self-Care Inventory-Revised questionnaire (SCI-R). The Spanish version will be used to evaluate treatment adherence (Jansà, Vidal, Giménez, Conget, Galindo et al, 2013).	Baseline, post-treatment, 3 months, 6 months, 1 year
Personality	Personality through the Millon Clinical Multiaxial Inventory-III (MCMI-III) (Millon, Davis and Millon, 1997), Spanish version by Cardenal and Sánchez (2007)	Baseline

Through a structured interview, sociodemographic data, medication taken and healthy and harmful habits will be recorded, as well as previous Mental Health treatment and diabetes-related support.

Clinical data and glycemic control will be collected through the medical record form of the visit to the physician and the data provided by the participant.

The primary variable is depression. Depressive symptoms during the previous 2 weeks will be assessed through a self-administered 7-item questionnaire (0–3), the BDI-FS [43]. For the diagnosis of depression, the Structured Clinical Interview for Major Depression Episode of the DSM-V will be used [44].

Among the secondary variables, fear of hypoglycemia will be evaluated with the Fear of Hypoglycemia questionnaire (FH-15) [45], which consists of 15 negative items on a Likert-type scale (1–5), and diabetes-related distress using the Spanish version [46] of the Diabetes Distress Questionnaire (DDS) by Polonsky et al., [47] which has 16 Likert-type items (1–5). The DDS provides a total distress score and 4 specific scores: affective distress; distress associated with the doctor-patient relationship; regimen-related distress and interpersonal distress. Quality of life will be assessed with the Diabetes Quality of Life Questionnaire [48], which evaluates quality of life specifically in individuals with diabetes mellitus. The Spanish version [49] has 43 questions (1–5) and 4 subscales: Dissatisfaction, Impact, Social/vocational concern and Concern for future aspects. Anxiety will be addressed using the Spanish version [50] of the State-Trait Anxiety Inventory (STAI) [51]. The STAI consists of 2 scales: State Anxiety (STAI-S) and Trait Anxiety (STAI-T). Each scale includes 20 self-administered items (0–3). Coping will be evaluated with the Spanish version [52] of the COPE inventory [53], composed of 5 scales assessing problem-centered coping, another 5 scales measuring emotion-centered coping, and 3 scales measuring less useful coping responses. Adherence to treatment will be evaluated with the 15-item (1–5) Spanish version of the Diabetes Self-Care Inventory-Revised questionnaire [54]. Personality will be evaluated using the Millon Clinical Multiaxial Inventory-III Spanish version [55]. This questionnaire contains 175 items with true or false answers. It consists of 11 basic personality scales, 3 pathological characteristics scales, 7 moderate syndrome scales and 3 severe syndrome scales.

The results of the trial will be published in peer-reviewed journals and presented in conferences.

